### Regulation Statement

The study will be conducted according to the principles of the Declaration of Helsinki (7th revision, 64th World Medical Association General Assembly, Fortaleza, Brazil, October 2013) and in accordance with the Medical Research Involving Human Subjects Act (WMO).

## Results

For the retrospective study, the data collection has taken place and the database is complete. Results will be reported in March 2019. Enrollment of participants in the prospective study began in March 2017, and it was completed in December 2018. Data collection will be completed in December 2019. The first results will be reported in 2019.

## Discussion

The SPLENic Injury and Quality of life (SPLENIQ) study is the first study that examines the effect of traumatic spleen injury on patients’ QOL in both a retrospective and prospective observational study design. It also examines clinical and imaging outcome as well as cost-effectiveness. For several reasons, these studies add relevant information to the existing literature. First, there is a need for research into QOL after traumatic spleen injury, because this is an important but neglected factor in the trauma care literature. If more knowledge becomes available, this can be taken into account when choosing treatment. Second, the prospective study will be conducted in a multicenter context in 10 hospitals, involving a trauma surgeon and interventional radiologist in each hospital. This creates a strong collaboration between the participating hospitals and medical specialties, which hopefully adds to the inclusion rate. Third, it is still unknown what impact different SAE techniques and materials have on the morphology and volume of the spleen. To investigate this, using MRI is innovative and will provide interesting images containing important and necessary information.

Several factors related to the design and execution must be taken into account. First, patients will be treated with NOM, SAE, or surgery for a specific clinical condition. It may be the clinical situation that determines the long-term outcome, although that outcome is not or partially the result of the treatment. This risk is confounding by indication: the risk that the groups are in fact not easily comparable (ie, selection bias). To keep this to a minimum, the reason for choosing a particular treatment will be registered. In our analysis, we will correct for these confounding factors using propensity score analysis. Correction is only possible when adequate and good-quality information is available about the clinical condition of the patients, which led to the decision. The patient’s record will be searched thoroughly to find this information. Second, trauma patients often have multiple injuries that can affect QOL and clinical outcomes. We are not primarily interested in these additional injuries, but these will be included as a covariate in the analysis. Third, response bias may occur in the questionnaires group. Patients may decline participation because they are not interested or it may be too confronting to think/correspond about their psychological state. Fourth, the severely injured patients may be overrepresented in the nonresponse group concerning the questionnaires. To limit this, these patients will be visited as soon as they are approachable and, if necessary, will be provided assistance to complete the questionnaires. Fifth, the absence of randomization is a (strong) limitation and a potential source of bias, but randomized comparison in managing trauma patients is virtually impossible. Furthermore, it will have strong ethical implications as it is well known that randomizing trauma patients with intraabdominal bleeding, potentially unstable, is something not feasible in clinical practice. Sixth, the sample size calculation is based on the primary objective of the study. For the clinical and cost-effectiveness analysis, this implies that because of the small sample size, the uncertainty about the outcome is large. Seventh, we are aware of response shift bias. Response shift is a change in self-reported QOL that is a result of a change in internal standards (ie, recalibration), values (ie, reprioritization), or meaning of QOL (ie, reconceptualization) [56,57]. Thus, response shift reflects psychological adaptation: we do not consider this as a problem but as a fact of life. In addition, the method to prevent response shift contains recall bias itself. Considering this, and the fact that QOL is a generic outcome measure, ensures that we use the chosen method. Moreover, the retrospective patients will not be included in the prospective study.

In conclusion, the SPLENIQ study responds to the shortage of information about QOL after treatment for traumatic spleen injury. With developing a patient-oriented protocol, a necessary step is taken to customize standard care, which may contribute to a positive effect on QOL and clinical outcome.

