### Statistical Analysis

All analyses will be conducted using SPSS V24.0 (Statistical Package for Social Sciences, Chicago Illinois, USA). Frequencies and descriptive statistics will be calculated to provide an overview of the characteristics of the study population. Statistical test results will be considered significant at a level of *P*<.05.

Concerning the retrospective study, a MANCOVA will be done after correcting theoretically important covariates to assess the differences between treatment groups on the 4 WHOQOL-Bref domains and the general facet. For each type of treatment, a 1 sample *t* test will be performed for each WHOQOL-Bref scale to compare the QOL scores with reference data.

For both the retrospective and prospective studies, a logistic regression analysis will be performed on the outcome variables’ (1) need for reintervention (yes/no) and (2) for each complication (yes/no), assessing the effect of treatment after correcting for theoretically important covariates. With regard to hospital stay in days, a Kruskal-Wallis test will be performed with the group (type of treatment) and days in hospital. Analysis of covariance will be used to compare proximal versus distal SAE, thereby correcting the effect for theoretically important covariates. To confirm/find prognostic factors for failure of NOM, a logistic regression analysis will be performed if NOM is a failure quickly after treatment. Otherwise, a survival analysis will be performed.

Regarding the prospective study, to assess the differences between groups in their change in QOL over time, a linear mixed model analysis will be conducted. To answer our research question, we will focus on the interaction effect between measurement occasion and treatment group, while correcting for theoretically important covariates. For the repeated measures, an unstructured covariance matrix will be used. Item-level missing values will be imputed according to the guidelines of the questionnaires. Scale-level missing values will be handled directly through maximum likelihood estimation, because the mixed model procedure makes use of all available data for each participant over all time points.

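### The propensity score that the Discussion promises against confounding by indication is not carried by any analysis in the Statistical Analysis section, so hospital stay, and possibly the prospective test of change, are left uncorrected

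*Protocol article*

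**What the plan says.** The Discussion of the protocol article puts one threat first among its design limitations: "This risk is confounding by indication: the risk that the groups are in fact not easily comparable". It says that the reason for choosing a treatment will be recorded, and then names the remedy: "In our analysis, we will correct for these confounding factors using propensity score analysis". A little later in the same paragraph it turns to other trauma: "We are not primarily interested in these additional injuries, but these will be included as a covariate in the analysis".

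The Statistical Analysis section describes the treatment comparisons as follows.

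- Retrospective quality of life: "a MANCOVA will be done after correcting theoretically important covariates to assess the differences between treatment groups".
- Reintervention and each complication, in both cohorts: logistic regression, "assessing the effect of treatment after correcting for theoretically important covariates".
- Hospital stay: a Kruskal-Wallis test of days by type of treatment, with no adjustment stated.
- Proximal versus distal SAE: analysis of covariance, again with unnamed covariates.
- Prospective quality of life: a linear mixed model with an unstructured covariance, in which "we will focus on the interaction effect between measurement occasion and treatment group, while correcting for theoretically important covariates".

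The section does not mention a propensity score. The methods paragraph of the Abstract names only the multivariate analysis of covariance and mixed linear modeling.

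**The concern.** Treatment in this study follows the patient's condition. The Background says that NOM is standard for hemodynamically stable patients and that surgery is indicated in unstable patients who do not respond to transfusion. The Abstract adds injury severity and the preference of the hospital or doctor. A crude comparison of the three groups therefore mixes the effect of treatment with the effect of the condition that led to it.

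The authors see this and name a remedy, but the section that an analyst would carry out does not contain it. If that section is followed alone, the correction on which the Discussion relies is not made. Two comparisons are most exposed: hospital stay, which has no adjustment of any kind, and the prospective treatment-by-occasion interaction, where the stated adjustment may have no effect. The retrospective database is described in Results as already complete, so for that cohort an open choice of adjustment would be settled with the data in hand.

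**Working it through.** The plan gives no figure on this point. The check sets the sections side by side and asks, for each treatment comparison, whether the stated adjustment can change the result.

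**1. Where the score appears.** It appears once, in the Discussion. The Statistical Analysis section and the Abstract do not mention it. The Discussion does not say which analyses it covers.

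**2. Models in which main-effect covariates can act.** In the multivariate analysis of covariance, the logistic regressions and the proximal-versus-distal analysis of covariance, covariates entered as main effects alter the estimated group difference. These analyses have some correction, of a quality that depends on which covariates are chosen.

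**3. Hospital stay.** With n patients, group sizes n_j and rank sums R_j, the Kruskal-Wallis statistic is

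H = [12 / (n(n+1))] × Σ R_j²/n_j − 3(n+1).

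It uses only the ranks of days in hospital and the group labels. No covariate or score can enter it, and no weighting, matching or stratification is stated. As written, this comparison is uncorrected.

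**4. Prospective treatment-by-occasion interaction.** For patient i in group g(i), with five measurements and covariates x_i entered as main effects, the model is

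Y_i = μ_g(i) + 1·(x_i′γ) + e_i, with e_i ~ N(0, Σ) and Σ unstructured.

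Here μ_g holds the five free occasion means of group g. Let C be a 4 × 5 matrix of within-patient contrasts, with C·1 = 0.

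- Contrasts: C·Y_i ~ N(C·μ_g(i), CΣC′). The term x_i′γ has dropped out.
- Patient mean given the contrasts: mean(Y_i) given C·Y_i has expectation a_g(i) + x_i′γ + b′C·Y_i, with a_g, γ and b all free.

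The likelihood is the product of these two parts, and they share no parameters. The interaction is a function of C·μ_g only, so with complete data its maximum likelihood estimate is the raw difference between groups in mean change, whatever x_i contains. The same holds if x_i is a propensity score entered as a main effect.

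A simulation with 33 patients, 5 occasions and 3 groups agrees. Adding main-effect covariates changed the interaction contrasts by less than 1e-13, which is rounding error. When the covariate was allowed to interact with occasion, the contrasts did change.

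**5. When step 4 does not apply.** The estimate can move if measurements are missing, if covariate-by-occasion terms are included, or if patients are weighted. The Statistical Analysis section does not say in what form the covariates enter. Hence the prospective test may be uncorrected, rather than certainly is.

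**6. Why this matters for a test of change.** Main effects absorb differences in level between patients. They do not absorb a different course of recovery in the more severely injured. The first questionnaire is given after treatment, so recovery from the injury lies within the change being compared.

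**The case against.** The strongest objection is that nothing is contradicted. A propensity score can be a covariate in each of the regression models, or be combined with covariates by weighting or stratification. The Discussion itself plans a covariate for additional injuries beside the score, and nothing in the Statistical Analysis section excludes one. A reader might infer from the two sections that the methods are incompatible, but the documents do not support that.

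It is also fair that a journal article condenses its protocol. How the score is estimated and how it enters each model may be in a document not shown, and the absence of those details is no finding. What stands is narrower: the article specifies a test for hospital stay that cannot take the promised correction, and for the prospective primary test it states an adjustment that may do nothing.

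Two further inferences are tempting and should be left out.

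- *That direct adjustment is too large for the prospective cohort while a score is not.* One can count 3 × 5 = 15 means, 5 × 6/2 = 15 covariance parameters and 10 degrees of freedom for the pre-treatment items under Clinical Data, giving 40 against the 33 patients in the sample size section. With a two-degree-of-freedom score the total is 32. But the covariates are not named, and 33 is the number required for power, not the number enrolled. Complete data from 33 patients would give 33 × 5 = 165 observations. Estimating a three-group score from the same 10 degrees of freedom itself takes 2 × (10 + 1) = 22 coefficients. The count does not favour either method.
- *That the score must outrank direct adjustment.* The Discussion promises a score but does not rank it above the covariates. The ranking is a matter of choice, provided it is made beforehand.

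**Conclusion.** The point holds in a limited form and should be corrected. The Discussion commits to a propensity score for the study's main bias, and no analysis in the Statistical Analysis section carries it. That hospital stay is uncorrected follows directly from the test named. That the prospective treatment-by-occasion estimate is uncorrected is conditional: it needs covariates entered only as main effects, complete data and the stated unstructured covariance. Under those conditions the adjustment changes the estimate by exactly zero.

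The size of the remaining bias cannot be calculated, because the article gives no distribution of prognostic factors by treatment group. The retrospective quality-of-life comparison and the logistic regressions do have covariate adjustment; for them the open matter is only how the score and the covariates fit together.

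**What to change.** Reconcile the two sections by writing the promised score into the Statistical Analysis section.

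- Specify a score for the three treatments, built only from pre-treatment variables, and check overlap between the groups before using it.
- Apply it in a form that can affect each comparison. In the mixed model this means weighting or score-by-occasion terms, not a score entered as a main effect alone.
- Replace or supplement the Kruskal-Wallis test with an adjusted or weighted comparison of hospital stay.
- State how the score relates to the covariate adjustment, for example with additional injuries as a covariate beside it, and name before analysis which result is primary.
- Let the overlap check decide whether the recorded reason for treatment belongs in the score, since it may nearly determine treatment and so remove the overlap.

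The cost is a change of wording and modest extra analysis. Patients without counterparts in the other groups will count for less. At the small prospective size the score will be imprecise, and the report should say so.

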## Abbreviations

CT: computed tomography
EQ-5D-5L: Euroqol 5-Dimensional 5-Level questionnaire
ETZ: Elisabeth-TweeSteden Ziekenhuis
FAST: focused assessment with sonography in trauma
iMCQ: iMTA Medical Consumption Questionnaire
iMTA: Institute for Medical Technology Assessment
iPCQ: iMTA Productivity Cost Questionnaire
MANCOVA: multivariate analysis of covariance
MCID: minimal clinically important difference
MCS: summary scores for the mental component (SF-12)
METC: Medical Ethical Committee
MRI: magnetic resonance imaging
NOM: nonoperative management
PCS: summary scores for the physical component (SF-12)
QOL: quality of life
SAE: splenic artery embolization
SF-12: 12-Item Short-Form Health Survey
SF-36: 36-Item Short-Form Health Survey
SPLENIQ: SPLENic Injury and Quality of life
US: ultrasound
WHOQOL-Bref: World Health Organization Quality of Life assessment instrument-Bref

## Appendix

Multimedia Appendix 1 Peer-reviewer report 1 from ZonMw.

Multimedia Appendix 2 Peer-reviewer report 2 from ZonMw.

Multimedia Appendix 3 Peer-reviewer report 3 from ZonMw.
